### Experimental Protocol

***Objective i - ***The first phase of the proposed work (Phase I) will involve two laboratory-based examinations of the acute metabolic and behavioural responses to extended fasting relative to ingestion of a standardised breakfast. These trials will be applied in a randomised and counterbalanced order with 3-28 days interval except for eumenorrheic women, whose trials will be separated by 28 ± 2 days and only at least 3 and at most 10 days after the onset of menses (i.e. follicular phase) to ensure that the effects of menstrual cycle on the majority of hormones and therefore resting metabolic rate (RMR) and appetite will be both minimal and standardised between trials [69-71]. These acute trials will be conducted in our resting metabolism laboratory in accordance with current guidelines for best practice in measuring resting metabolic rate [72]. Most notably, ambient temperature in this laboratory is maintained between 20 and 25°C (with intra-individual trials standardised within 2°C) and participants will arrive for testing at 8 am (±1 h) in a 10 hour fasted state but having ingested 1 pint of plain water upon waking following standardised physical activity and diet (the latter to incorporate either daily breakfast or extended fasting according to the group randomisation described later, thus permitting meaningful comparisons with follow-up visits). Repeated 5 minute resting expired gas samples will be collected over 30 minutes (after 20 minutes of quiet rest) to establish RMR and substrate selection before a cannula will be fitted to an antecubital vein for the acquisition of a baseline 15 ml blood sample, along with further samples throughout that day.

At this stage, participants will provide ratings of hunger and appetite using validated visual analogue scales [73], for subsequent follow-up post-breakfast and also pre-post lunch and at the end of day. They will then receive either no breakfast or a typical standardised breakfast (composed of cereal, toast and orange juice) with the opposite treatment applied in each participant's second trial). The specific food and macronutrient composition of this breakfast has been described previously [74] and provides quantities intended to deliver 14 mg carbohydrate per kJ of each individual's previously established RMR. Fifteen minutes later or upon completion of the breakfast (if longer than 15 minutes is required) a 3 hour post-prandial period will commence, involving collection of all urine output (for determination of urea nitrogen excretion) with hourly expired 5 minute gas samples to assess changes in substrate metabolism (i.e. carbohydrate, lipid and protein oxidation) and DIT (i.e. post-prandial energy expenditure minus RMR). Fifteen millilitre blood samples (including 5 ml waste) will also be drawn 15, 30 & 60 minutes post-breakfast, then at hourly intervals to determine systemic concentrations of: glucose; lactate; insulin; NEFA; urea; 'energy balance hormones' that are known to play a central role in the regulation of metabolic rate, appetite and spontaneous physical activity (e.g. free thyroxine, adiponectin, CCK, total/acylated ghrelin, leptin & PYY); and also cytokine concentrations (e.g. interleukin-6 and TNF-α), in view of recently documented differences in post-prandial inflammatory responses to varied meals across different populations [75] (with low/high density lipoprotein cholesterol and CRP only followed-up at the 3 hour time-point). Participants will then be provided with a test meal of standardised composition (1 kg cooked Sainsbury's™ penne pasta and Ragu™ traditional tomato sauce; prepared at a ratio of 1:1 uncooked mass) along with *ad libitum *plain water (although participants will ingest the same volume of water as in their first trial during all subsequent visits), which we have previously employed during pilot work to estimate likely differences in voluntary energy intake. At this stage, participants will be left alone in the laboratory and receive a recorded message stating: "We ask that you continue eating until you have satisfied your hunger. The lunch will remain in front of your for at least 30 minutes, at which point the post-lunch timer will be started, although you will be allowed to continue eating if you are still hungry."

The bowl of pasta will be refilled every 10 minutes to minimise any visual feedback in the regulation of appetite. To gain additional insight regarding psychological reward and food hedonics, a validated labelled magnitude scale [76] will be administered following the first and last mouthful of this meal to reliably assess the degree of 'pleasantness' associated with ingestive behaviour. The 3 hour post-prandial period will then be repeated exactly as following breakfast (but without the 15-30 minute samples) to track metabolic responses to lunch.

***Objective ii - ***Phase II of testing will commence within 3-28 days after completion of each participants' second trial under Phase I of testing (thus using participants' breakfast trial along with the measures described above as a baseline). This trial schedule will again be used for all participants other than for eumenorrheic women, who will follow the same restrictions as described above and therefore occasionally be required to complete their first trial under Phase II prior to the completing the second trial under Phase I. In such cases, these participants' 6-week intervention will simply be deferred for two weeks (i.e. enabling completion of Phase I) to allow follow-up measures to be taken at the same stage in the menstrual cycle. The first visit under Phase II will begin with participants again arriving in the laboratory at 8 am (±1 h) having adhered to the same standardisation procedures as described for Phase I. Measurements of body mass and adiposity based on hip and waist circumference (i.e. widest gluteal girth & mid-point between lowest rib and iliac crest, respectively), sagittal abdominal height (using a Holtain-Kahn calliper at the iliac crest) and body composition via DEXA (Hologic Discovery W) will also be made at this visit, before a small (~1 g) sample of subcutaneous adipose tissue will be acquired using a 14 G needle to determine basal expression of key genes related to appetite and physical activity regulation (e.g. adiponectin and leptin) and energy expenditure (e.g. UCPs).

This second phase of data collection will involve each participant being randomly assigned either to an extended daily fasting group (only plain water permitted until 1200 each day) or a breakfast consumption group (prescribed intake of ≥3000 kJ before 1100 each day, to include at least 1500 kJ within two hours of waking) for a period of 6 weeks [a duration previously shown to be sufficient for dietary modification to induce detectable changes in energy balance and body composition; [35]. To facilitate this process, participants assigned to the breakfast group will be provided with detailed examples of appropriately energetic breakfasts and the energy content of other typical breakfast foods, although the breakfasts consumed will ultimately be self-selected by each individual on a daily basis. Upon completion of this 6 week dietary modification, participants will return to the laboratory for follow-up of all anthropometric measures and a second subcutaneous adipose tissue biopsy to determine whether the intervention has altered the expression of those genes measured at baseline (described above).

In relation to the stated objectives, this design therefore examines whether and how any acute alterations in energy balance can culminate in chronic changes in energy balance (i.e. the acute effects of each treatment may be modified as participants become accustomed and adapt to it). To further inform such questions, during the first and last week of the intervention participants will maintain detailed weighed records of their habitual food and fluid intakes for subsequent analysis of daily energy and macro-nutrient intakes using dietary analysis software (CompEat Pro). Additional data regarding feeding patterns will be gathered via analysis of time of day, daily frequency and energy content of individual eating occasions, with meals defined as ingestion of ≥1256 kJ at any given eating occasion and snacks defined as ingestion of <1256 kJ more than 45 minutes before or after a meal [77]. All participants will receive telephone reminders to ensure appropriate compliance to the dietary record process, as has been advocated and applied to good effect by others [24]. The food diaries provided to participants will also be accompanied by the same validated labelled magnitude scale [76] that participants will have used during the first phase of testing to provide a rating of 'pleasantness' following the first and last mouthful of their lunchtime meal, thus informing research questions regarding psychological reward and food hedonics. Concurrent to these two periods of dietary recording, participants will also be fitted with a combined heart-rate/accelerometer (Actiheart, CamNtech) in order to accurately record energy expenditure/physical activity habits [54,55] for the entire duration of each 7 day assessment period (which will also be complemented by daily records of participants physical in/activities and sleep/waking times). Importantly, at the point when this physical activity monitor is fitted, participants will be provided the following message both verbally and in writing to ensure that only genuinely meaningful behavioural responses are recorded: "Your lifestyle choices during this free-living monitoring period are central to this study. We are interested in any natural changes in your diet and/or physical activity habits, which you may or may not make in response to the intervention. This monitoring period has been carefully scheduled to avoid any pre-planned changes in these habits, such as a holiday or diet/exercise plan. You should inform us immediately if unforeseen factors external to the study may influence your lifestyle."

After each participant's follow-up trial under Phase II, participants will continue adhering to their assigned intervention for at least 2 days to allow for the 48 hour dietary control (although up to 7 days will be permitted in participants for whom either the menstrual cycle need not be controlled for or when both trials can still occur within the follicular phase) before returning to the laboratory to repeat their breakfast trial exactly as described in relation to Objective i. This trial will therefore inform whether acute metabolic and/or behavioural effects may be modified following chronic exposure to each treatment. A formal exit interview will also be incorporated into this final visit during the afternoon post-prandial period to obtain qualitative data regarding participants' experiences of the study and motives for any perceived changes in behaviour.

***Objective iii - ***In relation to this objective, relevant data will be gathered during the second phase of testing to explore how interactions between extended daily fasting may relate to insulin resistance and cardiovascular disease risk (whether related to or independent of changes in energy balance). From a whole-body perspective, highly relevant data will be gathered during the first and last week of the 6 week intervention using a subcutaneous continuous glucose monitor (iPro, Medtronic) to record 24 hour glucose profiles for each participant (thus revealing whether either treatment alters either the average daily glucose concentration or the magnitude of hyperglycaemic excursions following meals). This real-world indication of glycaemic control will be complimented not only by simple comparison of changes in fasted glucose/insulin concentrations changes over the 6 weeks but also by way of an oral glucose tolerance test (OGTT) that will be conducted at baseline and follow-up in Phase II, immediately following each adipose tissue sample. At a more reductionist level, the adipose tissue samples will be subjected to further analysis to determine the sensitivity of this particular tissue to insulin. Specifically, on the day that these samples are collected, adipocytes will be isolated by collagenase digestion before determination of [U-^14^C]-D-glucose uptake at basal, submaximal (50 pmol•l^-1^) and maximal (20 nmol•l^-1^) insulin concentrations. This glucose uptake assay has been shown to accurately reflect 3-O-methylglucose transport under the conditions described [78,79] and the resultant data will be expressed both as pmol•min^-1 ^relative both to lipid mass [80] and, following analysis of cell size, to cell surface area. This will be in addition to subsequent analyses for the total protein content of GLUT4 and Akt in this tissue and the expression of key genes implicated in lipolysis (e.g. HSL and ATGL), lipogenesis (e.g. PPARγ, PGC1a, SREBP1c) and more generally in glucose uptake and oxidation (e.g. GLUT4, PDK4, AMPKα-1/2, resistin, RBP4, leptin and adiponectin) and/or insulin signalling (e.g. IRS1/2, PI3K, Akt and TBC1 domain family member 4), thus informing whether there is any adaptive response to the intervention at the level of adipose tissue gene expression and protein content.

Finally, in relation to cardiovascular disease risk, measurements of blood lipid profiles, cytokine responses, CRP and blood pressure (DINAMAP Pro 100-400 V2, UK) will be contrasted between participants' baseline and final follow-up trials, as will the expression of other relevant genes in adipose tissue samples (e.g. interleukin-6 and TNF-α). All hormones/cytokines to be measured in the proposed work will be quantified via ELISA, with whole blood glucose determined using a YSI analyser, plasma glucose, NEFA, cholesterol and urea measured using a spectrophotometer and gene expression using TaqMan^® ^Real-Time PCR.

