### Trial Design

***Objective i ***will be addressed by way of an acute randomised cross-over comparison while ***Objective ii ***and ***Objective iii ***will be addressed via a chronic independent comparison of two parallel and randomly assigned groups, both involving a contrast between daily breakfast consumption and extended fasting. Figure 2 illustrates the course of progress through this trial consistent with current CONSORT guidelines for reporting randomised trials [63].

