### Statistical Approach/Power Estimation

The number of research participants to be recruited was estimated based upon a worthwhile effect dictated by the smallest shift in energy balance necessary to induce chronic weight loss. Specifically, one of the most similar studies to the proposed work applied doubly-labelled water to measure average daily energy expenditure in a population not dissimilar to that planned [38], from which a mean of ~12000 kJ·d^-1 ^might be expected with a standard deviation in the region of ~2000 kJ·d^-1^. The daily breakfast to be consumed in this trial will provide in excess of ~3000 kJ·d^-1 ^and our pilot work using this breakfast indicates that this is likely to stimulate metabolism in the lead up to lunch by ~150 kJ·d^-1 ^and reduce energy intake at lunch by ~150 kJ·d^-1^, relative to continued fasting. Therefore, for breakfast consumption to exert a worthwhile effect on net energy balance (i.e. sufficient to compensate for the energy it provides directly), physical activity energy expenditure would need to increase and/or subsequent energy intake to decrease by a further 2700 kJ·d^-1^. Using the above figures, a worthwhile increase in energy expenditure would require ~14 participants in each treatment group to confer a 90% probability of detecting such an effect statistically using a two-tailed *t*-test with an alpha level of 0.05. A total of 70 participants will therefore be recruited for the main study treatment arms in view of the 14% drop-out rate reported by Schlundt *et al*. (1992) when placing similar demands on volunteers [51], thus aiming to achieve at least 60 participants to provide sufficient statistical power even when the overall breakfast *versus *no breakfast groups are stratified according to FMI (with baseline breakfast habits, gender and age included as co-variates in the analysis). Nonetheless, to minimise the negative impact of loss to follow-up on validity, participants will be advised at trial enrolment to very carefully consider the required investment of time and effort relative to their current and forthcoming commitments outside of the trial, such that exclusions based on likely withdrawal can be made prior to randomisation [68]. Any unforeseen circumstances or withdrawal of consent subsequently resulting in loss to follow-up will be documented fully in the final trial report. Data collected from these individuals to the point of loss will then be compared with those who complete each treatment to determine whether the overall conclusions of the trial may be generalised beyond populations reflective of the latter (i.e. to anyone willing to be randomised).

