
As with the primary outcome measure, secondary variables will also be analysed using either paired or independent *t*-tests applied to simple summary statistics between groups or trials, respectively (e.g. fasted/peak values, incremental area under curve, average value over 24 h, *etc*.). Given that these sample size estimations are based on a primary outcome that inherently displays a relatively large inter-individual variability, it is anticipated that the more consistent responses of secondary variables will also be detectable with the selected sample size.

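### Phase I is a cross-over with randomised visit order, but its t-test has no period term: the paired test is valid, yet a period term would protect power at almost no cost

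*Protocol article*

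**What the plan says.** Trial Design says that Objective i "will be addressed by way of an acute randomised cross-over comparison". Experimental Protocol adds: "These trials will be applied in a randomised and counterbalanced order with 3-28 days interval". Eumenorrheic women have a fixed spacing of 28 ± 2 days.

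The analysis is in the second paragraph of Statistical Approach/Power Estimation: "secondary variables will also be analysed using either paired or independent *t*-tests applied to simple summary statistics between groups or trials, respectively". No period, order or sequence term is named anywhere in the article. The covariates it does name ("with baseline breakfast habits, gender and age included as co-variates in the analysis") do not include visit order, and the sentence ties them to the comparison of the randomised groups within fat-mass-index strata.

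The only sample-size calculation concerns the parallel-group energy-expenditure outcome. For secondary variables, the article only expects that effects will be detectable with the same numbers. It gives no within-person SD, visit effect or power for Objective i.

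**The concern.** Randomising and counterbalancing visit order stops a first-to-second-visit change from being mistaken for a breakfast effect. A paired t-test uses only part of that design. It treats all breakfast-minus-fasting differences as having one common mean. If visits differ systematically, those differences centre on one value in participants who had breakfast first and on another in those who fasted first. The gap between the two values is then counted as random error.

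At stake is the precision of the Objective i comparisons. If the two sequences end up unequal in size, a small bias is added. This is not detail left to an unseen analysis plan: the article names the test, and that test leaves out a factor the design randomises.

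The sentence that names the test also has a wording fault. The order of its two lists, joined by *respectively*, pairs independent t-tests with trials and paired t-tests with groups, the reverse of what the design calls for.

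**Working it through.** **The plan's own figure.** Inputs from Statistical Approach/Power Estimation: difference 2700 kJ/d, SD about 2000 kJ/d ("with a standard deviation in the region of ~2000 kJ·d^-1"), two-sided alpha 0.05, 90% power.

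- n per group = 2 × (1.960 + 1.282)² × (2000/2700)² = 2 × 10.51 × 0.549 ≈ 11.5, so 12 by the normal formula.
- With the exact t distribution, 13 per group gives 91.0% and 14 gives 93.0%. The stated figure of about 14 is reproduced within two participants.
- Drop-out: 60 / (1 − 0.14) = 69.8, so 70, as stated.

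These figures concern the parallel groups. They say nothing about Objective i, so what follows rests on assumptions.

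**Model for Phase I.** Let D be a participant's breakfast-minus-fasting difference, with random SD 1 (so effects are in SDs of the within-person difference). Let τ be the treatment effect and π the second-minus-first-visit effect.

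- Fasting first: mean D = τ + π. Breakfast first: mean D = τ − π.
- Equal sequences: the overall mean of D is τ, so there is no bias.
- The variance that the paired test estimates is 1 + π² × N/(N − 1), although the mean of D really varies with variance 1/N.
- Period-adjusted test: average the two sequence means of D, with SE = s_pooled × ½ × √(1/n₁ + 1/n₂) on N − 2 degrees of freedom. π drops out of both the estimate and the error.

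**Power, equal sequences.** Assumed: N = 60 (30 per sequence) and τ = 0.368, which gives 80% power with the period term. By hand, paired-test power ≈ Φ(τ√N − t × √(1 + π²N/(N − 1))), with τ√N = 0.368 × 7.746 = 2.85 and t = 2.00 (59 df). The simulation used 50,000 runs per setting.

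| π (SD) | Error variance | By hand | Paired, simulated | Period-adjusted, simulated |
|---|---|---|---|---|
| 0 | 1.000 | Φ(0.85) = 80% | 80.1% | 80.1% |
| 0.2 | 1.041 | Φ(0.81) = 79% | 79.1% | 80.2% |
| 0.3 | 1.092 | Φ(0.76) = 78% | 77.5% | 80.1% |
| 0.5 | 1.254 | Φ(0.61) = 73% | 73.1% | 80.2% |

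From a 90% base, the paired test gives 89.4%, 88.5% and 85.3% at π = 0.2, 0.3 and 0.5. With N = 30 and an 80% base, it gives 78.9%, 77.6% and 72.6%. When there is no treatment effect, its simulated false-positive rate at N = 60 is 4.9% at π = 0 and 3.0% at π = 0.5: conservative, not inflated.

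**Unequal sequences.** The unadjusted mean of D is biased by π × (n₁ − n₂)/(n₁ + n₂):

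- 33:27 gives 6/60 = 10% of π
- 35:25 gives 10/60 = 17% of π

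At π = 0.5 these are 0.05 and 0.08 SD.

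**The literal reading of *respectively*.** Testing paired trials as independent multiplies the error variance by 1/(1 − ρ), where ρ is the within-person correlation. For assumed ρ of 0.5 and 0.8, that is 2 and 5 times.

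**The case against.** The strongest reply is that nothing here is an error. A paired t-test on a counterbalanced two-visit design is unbiased and, if anything, conservative. No power is claimed for Objective i, so none is missed. The loss depends on a visit effect that the article never mentions, and it is negligible when that effect is small. The article also standardises room temperature, arrival time, fasting, prior diet and activity, and menstrual phase between visits. All of this stands, and it is why the point is one of efficiency only.

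Four stronger readings are tempting but not supported:

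- *Objective i is underpowered.* The article gives neither a target power nor a visit effect for it.
- *The article itself shows that the visits differ.* At the test lunch, "participants will ingest the same volume of water as in their first trial during all subsequent visits". That makes the volume drunk the same at both visits, so it is standardisation and not evidence of a visit effect. Nor does the article say that the laboratory procedures are new to participants at the first visit.
- *The false-positive rate rises.* It needs a marked imbalance. If 70 start 35:35 (an assumption) and 10 drop out, the worst split is 35:25, with about 6% false positives at a visit effect of 0.5 SD. At 33:27 the rate is about 4%. If drop-out is random, 34:26 or worse has a chance of about 1.3%.
- *Phase II is biased.* The Phase I breakfast trial does serve as baseline ("thus using participants' breakfast trial along with the measures described above as a baseline"), and it is a first visit for some participants and a second for others. But arm and Phase I order are both randomised, so order balances across arms in expectation. At most it adds noise, of a size the article does not allow one to calculate.

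**Conclusion.** The point holds as a minor, free improvement. The article prescribes a t-test that ignores the visit order its own design randomises. With equal sequences, the paired test remains unbiased and valid. A period term costs nothing measurable if visits do not differ (80.1% power either way at N = 60), and it recovers about 1, 2.5 or 7 percentage points if the visit effect is 0.2, 0.3 or 0.5 SD of the within-person difference. It also removes the small bias that unequal sequences would bring. These sizes rest on assumed visit effects, on 60 participants completing both visits and on an 80% base. No figure in the article is shown to be wrong.

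The reversed pairing under *respectively* is probably a slip of word order. It is still worth correcting, because a literal reading would cost more than the missing period term.

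**What to change.** Reword the analysis sentence in the second paragraph of Statistical Approach/Power Estimation to say:

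- Phase I outcomes are analysed within participant as a two-period cross-over, with period as a fixed effect. Equivalently, the two sequences are compared on second-minus-first-visit differences, and half the contrast between sequences estimates the treatment effect.
- Independent-samples comparisons apply to the randomised groups and within-participant comparisons to the trials, so that *respectively* no longer reverses them.

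Optionally, include Phase I sequence as a term when the final breakfast trial is compared between arms against the Phase I breakfast trial.

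The cost is one sentence and one degree of freedom. Visit order is part of the randomised design, so no new data, visits or participants are needed.

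### For fasted secondary outcomes the plan names the Phase I breakfast trial as baseline, although both Phase I trials give an equivalent pre-meal value; averaging the two would gain precision at no cost

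*Protocol article*

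**What the plan says.** All of the following is in the Protocol article, Experimental Protocol.

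- **Two trials before the intervention (Objective i).** Phase I "will involve two laboratory-based examinations of the acute metabolic and behavioural responses to extended fasting relative to ingestion of a standardised breakfast", in randomised, counterbalanced order. When the menstrual cycle forces a different visit order, the intervention is deferred so that Phase I is still completed first (Objective ii).
- **Same preparation both times (Objective i).** For these trials "participants will arrive for testing at 8 am (±1 h) in a 10 hour fasted state", after standardised activity and diet, "the latter to incorporate either daily breakfast or extended fasting according to the group randomisation described later". A participant's preparation is therefore the same before both trials.
- **Fasted measures come first (Objective i).** Expired gas for RMR and substrate oxidation is collected first, "before a cannula will be fitted to an antecubital vein for the acquisition of a baseline 15 ml blood sample". Appetite ratings follow, and only then is breakfast given or withheld.
- **Baseline (Objective ii).** Phase II follows Phase I, "thus using participants' breakfast trial along with the measures described above as a baseline". At the end of the intervention only the breakfast trial is repeated.
- **Use of the baseline (Objective iii).** There is to be a "simple comparison of changes in fasted glucose/insulin concentrations changes over the 6 weeks", and the cardiovascular markers "will be contrasted between participants' baseline and final follow-up trials".
- **Analysis (Statistical Approach/Power Estimation).** Secondary variables are compared by t-tests on simple summaries, with fasted values among the examples.

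**The concern.** Pairing breakfast trial with breakfast trial is needed for anything measured after the meal. That reason does not extend to values taken before the meal. For RMR, fasting substrate oxidation and fasted blood markers, the two Phase I trials are replicate pre-intervention measurements, yet the text names one of them as the baseline.

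A single fasted value carries day-to-day variation into the between-arm comparison of change. Because trial order is randomised, the breakfast trial is also the first visit for about half the participants and the second for the rest, so any first-visit shift adds some spread. The document gives no figure for such a shift.

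At stake is the precision of secondary outcomes serving Objectives ii and iii. These have no power calculation of their own; the plan only expects them to be detectable with the chosen sample. With at least 60 completers split by treatment and by fat-mass index, about 60/4 = 15 remain per arm in each stratum, so precision that costs nothing is worth having.

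**Working it through.** **The plan's own figure.** Inputs from Statistical Approach/Power Estimation: difference 2700 kJ/d, SD 2000 kJ/d, two-sided alpha 0.05, power 90%.

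- Normal approximation: n = 2 × (1.960 + 1.282)² × 2000²/2700² ≈ 11.5, so 12 per group. The noncentral t gives 12.6, so 13.
- The plan states about 14, where t-test power is 93.0%.
- Drop-out: 60/(1 − 0.14) = 69.8, so 70.

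The stated sample size reproduces. It concerns free-living energy expenditure and does not depend on the laboratory baseline.

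**Value of the second fasted baseline.** The document gives no between-visit correlations, so these are assumptions. Set the outcome variance to 1 at every visit. Let *b* be the correlation between the two Phase I values and *r* the correlation of each with follow-up.

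- Change score, one baseline: 2(1 − r)
- Change score, mean of two: 1 + (1 + b)/2 − 2r
- Covariate, one baseline: 1 − r²
- Covariate, mean of two: 1 − r²/[(1 + b)/2]

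*Equal correlation (b = r).* The change-score variance with two baselines becomes 1.5(1 − r). The ratio to one baseline is 0.75 at any r: 25% lower variance, a standard error 13.4% smaller, and the equivalent of 60/0.75 = 80 completers rather than 60.

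| r = b | Covariate, one | Covariate, two | Fall |
|---|---|---|---|
| 0.5 | 0.750 | 0.667 | 11% |
| 0.7 | 0.510 | 0.424 | 17% |
| 0.9 | 0.190 | 0.147 | 22% |

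A simulation at r = 0.8 agreed with the formulas: change-score variance 0.399 against 0.299, covariate-adjusted variance 0.359 against 0.288. At r = 0.8, 30 per arm and 90% power, the detectable difference in change moves from 3.242 × √(2 × 0.4/30) = 0.53 SD to 3.242 × √(2 × 0.3/30) = 0.46 SD.

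*Baselines closer to each other than to follow-up (b > r).* The Phase I trials are 3-28 days apart. Follow-up comes after a further gap and a 6-week intervention, so this case is plausible.

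- b = 0.9, r = 0.7, change score: 0.60 to 1 + 0.95 − 1.40 = 0.55, a fall of 8% (60 × 0.60/0.55 ≈ 65 equivalent completers).
- b = 0.9, r = 0.7, covariate: 0.510 to 1 − 0.49/0.95 = 0.484, a fall of 5%.
- b = 0.8, r = 0.7, change score: 0.60 to 1 + 0.90 − 1.40 = 0.50, a fall of 17%.

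*No baseline in the analysis.* If follow-up values are compared directly, the gain is zero.

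**The case against.** The strongest reply is that the baseline wording sits in a parenthesis about scheduling. It explains why no further pre-intervention meal test is needed, and nothing in the article excludes the fasting trial's pre-meal values. They are in any case used in the Objective i crossover. How to combine duplicate baselines is often left to an analysis plan, and a single standardised baseline is valid in a randomised comparison.

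Much of this stands. A reader might infer that the second value is discarded, but the text says neither that it is dropped nor that it is pooled, and the reference to the other measures described is ambiguous. The reply does not remove the point, because the article does not leave the baseline open: it names one trial, for a reason that applies only to post-meal outcomes.

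Three further limits also stand:

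- **Fasted glucose and insulin.** The Phase II baseline visit includes an oral glucose tolerance test (OGTT), which may supply another fasted value. The Objective iii text does not tie these two markers to the breakfast trial.
- **Appetite ratings.** No blinding to the meal is described, and the second trial is always the opposite treatment. Participants may anticipate a meal or a fast, so the two pre-meal ratings may not be equivalent.
- **Equal correlation.** The 25% figure depends on it, and the visit timing suggests a smaller gain.

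**Conclusion.** The point holds as a free improvement in efficiency for RMR, fasting substrate oxidation and fasted blood markers. It is not an error that biases the comparison. It leaves free-living energy expenditure, the sample size and all post-meal outcomes unaffected.

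The 25% fall in change-score variance belongs at the upper end, and 8% is a plausible smaller value. The covariate range of roughly 5-22% covers the cases worked above. All of these rest on assumed correlations and equal variances.

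Two stronger readings are tempting and unsupported. One is that half of the baseline information is lost. That is true only as a count of measurements: under equal correlation the variance of the baseline value itself falls by (1 − r)/2, which is 10% at r = 0.8. The other is that precision suffers under any analysis. The planned t-tests on fasted values could be run on follow-up values alone, and baseline precision would then be irrelevant.

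**What to change.** Add one sentence to the baseline definition under Objective ii, or to the analysis plan. For RMR, fasting substrate use and fasted blood markers, baseline is the mean of the two Phase I pre-meal values, or the single value if one is missing. It enters the change score or, preferably, the model as a covariate. For post-meal outcomes and for appetite ratings, baseline remains the breakfast trial alone. For fasted glucose and insulin, say also whether a fasted sample from the Phase II OGTT visit, if one is drawn, forms part of the baseline.

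The cost is a line of wording. No visit, sample or participant is added, since both sets of measurements are already scheduled.
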